### Study population

In this trial, the intervention will target clusters, where a cluster is defined as a group of EMR—capable facilities within a specific geographical proximity. Outcome parameters will be assessed at the patient level.

Two recruitment strategies will be used to enroll participants:

Line listing—a central EMR database will provide a line list of all AYP in the participating EMR sites. Random number sequences will be used to select eligible participants at each facility, with allowances for refusals.Weekly appointment diaries—a weekly diary will be used to list AYP scheduled for clinic visits in the coming week. Eligible participants will be randomly selected using a random number sequence.

Selected participants will be invited to an open-day activity for recruitment, where informed consent will be obtained. These recruitment strategies will continue until the required sample size is reached.

Measurements will be taken on the same cohort at the end of each intervention step as clusters move from the control to active intervention phases (Table 2).

### Intervention

The myCareHub portal will be available on both the Google Play Store and iOS App Store. Developed by the study team with significant input from end users, it is designed to facilitate behavior change using the COM-B framework (Figs 2 and 3). The portal comprises two mobile-based applications: a patient portal and an HCP portal, offering a range of features critical to supporting patients and providers in HIV care.

### Patient portal

Key features available to patients include:

E-learning resources—text, audio, and video content focusing on HIV treatment literacy, disclosure support, adherence support, sexual and reproductive health, and coping skills.Online communities—peer-to-peer networking and learning platforms to foster interaction and support among patients.Patient diary—a tool for self-monitoring, allowing patients to view their medical data from the facility’s EMR, record their experiences, and share relevant information with HCPs.Patient-reported outcomes—web forms and survey tools that capture patient-reported outcomes, triggering service requests in the HCP portal, ensuring timely and personalized care.Notifications—in-app and short message service (SMS) notifications for appointments and other reminders.Appointment rescheduling—this feature, to be developed in the second phase, will allow patients to reschedule appointments.

### Healthcare provider portal

The health care provider (HCP**)** portal will provide healthcare providers with tools to:

Track and monitor patient treatment, adherence, and symptoms.Offer personalized care based on data from the patient’s diary.Access patient data—the portal is synchronized with the facility’s EMR, allowing HCPs to access longitudinal patient visit data, lab results, and other medical information.

To ensure optimal use, quarterly open forums will be conducted with both HCPs and patients. These sessions will facilitate access to all available features and capture qualitative end-user insights for further improvements.

### Outcome measures

Outcome parameters will be measured at the individual level at pre-specified time points: baseline, every 3 months, and end-line (Table 5). These measurements will be captured using digitized case report forms (CRFs) to ensure accuracy and consistency in data collection.

**Table 5 pdig.0000380.t005:** Summary of outcome variables and analysis measures.

Variable	Definition	Units	Source	Measurement Level	Measurement Period	Comparison Groups	Analysis
PAM	Patient activation measure	100-point scale	PAM-13	Individual	Baseline, 3, 6 and 9 months	Intervention versus Control	Mean change in PAM
Self-reported medication adherence	Estimate of adherence on 0–100% scale	Proportion	Visual analogue scale and adherence questionnaire	Individual	Baseline, 3, 6 and 9 months	Intervention versus Control	% adherence
Viral load suppression (VLS)	Proportion with viral load below detection limit	Proportion	Electronic medical record	Individual	Baseline, 3, 6 and 9 months	Intervention versus Control	% VLS
Cluster retention	Active in care at the end of reporting period/active at the beginning of the period*100	Proportion	Program data	Cluster	Baseline, 3, 6 and 9 months	Intervention versus Control	% retention
Cluster VLS	Percent viral load suppression within cluster	Proportion	Program data	Cluster	Baseline, 3, 6 and 9 months	Intervention versus Control	% VLS
Mobile health application usability score	Numerical score	Mean score	mHealth App Usability Questionnaire (MAUQ)	Individual	End-point	Intervention	Mean scores
Mobile health service acceptability score	Likert-like scale and text	Sub-section scores	Custom acceptability tool	Individual	End-point	Intervention	Mean scores
Social support	Six questions on social supporters	Number of supporters and ratings of support	Social support questionnaire-6 item (SSQ-6)	Individual	Baseline	Intervention	Baseline SSQ-6 scores
Tuberculosis (TB) intensified case finding tool (ICF)	4 questions each scoring 0 or 1	0–4	Portal TB ICF tool, Paper-based TB ICF tool, Program reports	Individual	Continuous	Intervention versus Usual care	% cases diagnosed
							Median time to TB diagnosis
Screening for depression	9 questions each scored 0–3 for total possible score of 27	0–27	Portal patient health questionnaire (PHQ-9)	Individual	Continuous	Intervention versus Usual care	% cases diagnosed
Contraceptive use intention screening	4 questions	Yes/No	Portal screening tool	Individual	Continuous	Intervention versus Usual care	% users accessing contraceptives
Sexual and Gender Based Violence (SGBV) screening	4 screening questions	Yes/No	Portal SGBV screening tool	Individual	Continuous	Intervention versus Usual care	% survivors successfully identified
Alcohol and substance use disorder screening	6 screening questions	Yes/No, with score>2 indicating problem	Portal incorporated CRAFFT tool (Car, relax, alone, forget, friends, trouble)	Individual	Continuous	Intervention versus Usual care	% with alcohol use disorder identified
Online community engagement	User online activity and interactions	Usage logs, time spent on portal, feature usage	Analytical dashboard	Individual	Continuous	Intervention	Online engagement

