**Abbreviations**: TO–baseline, T1 –time period 1, T2 –time period 2, T3 –time period 3, T4 –time period 4. Mo–month. PAM–patient activation measure. VLS–viral load suppression. SSQ6- social support questionnaire short form. MAUQ–mHealth App usability questionnaire. TB ICF–tuberculosis intensified case finding. PHQ-9 –patient health questionnaire– 9 items, SGBV–sexual and gender-based violence, CRAFFT–car, relax, alone, forget, friends, trouble. **NB**: The third sequence is extended to ensure that the final stratum completes a minimum of six months, which is the recommended duration for adequately assessing patient activation.

To minimize heterogeneity between clusters, stratification was applied based on size (small, medium, large), sex (male, female), and viral load suppression (VLS). This stratification created comparable blocks of clusters prior to randomization, ensuring balance across the intervention groups (Table 3). Clusters were then randomly assigned to one of three sequences for the time of crossover from control to intervention using a computer-generated random number list (Table 4). Each cluster will begin in the control period and transition to the intervention at staggered intervals, with clusters randomized to groups of five or six. Each intervention sequence will last three months, with a two-week interval between sequences to allow for baseline measurements and smooth implementation of the intervention. The third sequence will extend for six months to allow for additional measurements (Table 2).

**Table 3 pdig.0000380.t003:** Sub-counties by key attributes.

Sub-county	Number of AYP ^b^	Size strata	VLS ^a^ 15–19	VLS 20–24	Cohort retention	Males (%)
Thika town	632	Large	80%	90%	89%	41%
Ruiru	330		84%	89%	68%	25%
Kiambu town	205	Medium	86%	89%	100%	32%
Kiambu Central	176		86%	90%	84%	55%
Gatundu South	166		61%	90%	50%	40%
Juja	146		91%	82%	67%	35%
Kiambaa	123		87%	91%	100%	27%
Kirinyaga South	116		91%	87%	88%	53%
Githunguri	113		85%	89%	100%	27%
Kabete	110		94%	94%	100%	23%
Gatundu North	107		92%	89%	100%	40%
Limuru	103		90%	100%	100%	35%
Kirinyaga West	88	Small	81%	92%	74%	37%
Kikuyu	73		100%	90%	100%	16%
Kirinyaga East	58		100%	86%	87%	57%
Lari	51		100%	91%	100%	23%
Kirinyaga North	50		60%	68%	88%	48%

^a^ viral load suppression

^b^ adolescents and young persons

**Table 4 pdig.0000380.t004:** Randomization of clusters into sequences.

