#### Viral load suppression and cluster retention

A customized data collection form will be used to extract individual viral load suppression status, cluster retention and cluster viral load suppression data from program reports and facility EMRs.

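### Table 5 defines cluster retention as a net head-count ratio, so patients entering care during a period can offset those lost

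*Protocol article*

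**What the plan says.** Table 5 in Outcome measures gives the definition of cluster retention as "Active in care at the end of reporting period/active at the beginning of the period*100". The rest of that row sets the unit, source, level, timing and comparison: "Proportion Program data Cluster Baseline, 3, 6 and 9 months Intervention versus Control % retention".

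The section Viral load suppression and cluster retention adds only where the figures come from. A form will extract "cluster retention and cluster viral load suppression data from program reports and facility EMRs". It has no rule for patients who start, transfer in or return during a period.

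Two other places touch on the subject. Study population states: "Measurements will be taken on the same cohort at the end of each intervention step". This describes repeated measurement of enrolled participants. Table 3, which lists sub-county attributes before randomisation, has a retention column under the header "VLS 20–24 Cohort retention Males", with no definition. Table 2 schedules cluster-level retention at every survey and, at T2 and T3, also lists retention as a separate item.

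**The concern.** A retention proportion normally follows a fixed group: of those in care at the start, how many are still in care at the end. The Table 5 formula instead compares two head-counts taken at different times, and the second may include people who were not in the first. Anyone entering care in between raises the figure, whether or not anyone was kept in care.

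Two things are at stake. The reported level of retention would be too high wherever patients enter, and a cluster that loses patients could appear to lose none. The planned comparison would also pick up any difference in entry between control and intervention time. Under Table 2, every cluster is in control at T0 and every cluster is in intervention at T3 and T4, so a change in entry over calendar time would partly coincide with exposure.

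**Working it through.** The article states no result, power or sample size for cluster retention, so there is no figure of its own to reproduce. The check is algebra on the printed formula.

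**Inputs**
- Formula, unit, source and comparison: Table 5.
- Loss and entry rates per period: not given. Assumed here as losses of 5% to 15% and entries of 0% to 20% of the starting number.

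**Formula.** Let S be the number active at the start, L the number of those who leave the count, and E the number who enter it and are active at the end.
- Printed ratio: (S − L + E)/S = (S − L)/S + E/S
- True retention: (S − L)/S
- Difference: E/S, the entry rate. The two agree only when E = 0.

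**Level.** Printed ratio for the assumed rates:

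| Loss | True retention | Entry 0% | Entry 5% | Entry 10% | Entry 15% | Entry 20% |
|---|---|---|---|---|---|---|
| 5% | 95% | 95% | 100% | 105% | 110% | 115% |
| 10% | 90% | 90% | 95% | 100% | 105% | 110% |
| 15% | 85% | 85% | 90% | 95% | 100% | 105% |

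Losses of 5%, 10% and 15% all appear as 100% when entries equal losses. Once entries exceed losses, the value passes 100%, which a proportion cannot do.

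**Contrast.** The bias in intervention minus control is the entry rate under intervention minus the entry rate under control.
- True retention 90% in both, entries 10% (intervention) versus 5% (control): 100% − 95% = +5 points, all spurious.
- True retention 90% in both, entries 5% versus 10%: 95% − 100% = −5 points.
- True retention 90% in both, entries 5% in each: 95% − 95% = 0.
- True retention 95% versus 90%, entries 3% versus 8%: 98% − 98% = 0, so a real 5-point difference disappears.

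**Is zero entry plausible?** The Introduction offers a rough national indication only. About 35% of 33,000 new infections is 11,550; divided by 160,000 young people living with HIV, this is 7.2% a year, or 1.8% a quarter. These are infections rather than clinic entries, and national rather than local, so the figure shows only that entry should not be presumed to be nil.

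**Does another section correct the formula?** No. The same-cohort sentence concerns measurements on enrolled participants, whereas this measure comes from programme data at cluster level. The data-source sentence gives no counting rule.

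**The case against.** The strongest reply is that the table cell is shorthand and a closed group was intended. The outcome is called retention and its unit is a proportion, both of which fit that reading. Table 3 lends some support: of its 17 values, ranging from 50% to 100%, 8 are exactly 100% and none is higher. A net head-count ratio would be expected to give some values above 100%, so that column looks closed or capped. Rules for transfers and returners are also the kind of detail an article may leave to a fuller document. The intention may well have been sound. But Table 3's column is undefined and differently named, and the article does more than omit detail: it prints a formula, and that formula does not give the quantity named.

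Several stronger readings are tempting but unsupported:
- A reader might infer that the comparison cannot measure retention at all. If entry is similar in the two conditions, the level is inflated but most of the bias cancels in the contrast.
- A reader might infer that the portal or the open days would draw in new patients and so look like better retention. Study population says that open days are for people selected from EMR line lists or appointment diaries, who are already in care. The article does not present the portal as a route into care.
- A reader might take the many 100% values in Table 3 as the error already at work. They are not evidence for it and, if anything, point the other way.
- A reader might count people turning 15 or 25 as a demonstrated source of bias. The Table 5 row does not say that the measure is limited to ages 15–24.

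The objection that little depends on this also stands. Cluster retention is not among the secondary outcomes named in the abstract or in Table 1.

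**Conclusion.** The point holds as a defect in a stated definition. Taken literally, the Table 5 measure is true retention plus the entry rate. That follows from the formula alone and needs no assumed figure.

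The size in this trial is unknown, because the article reports neither entries nor losses. The 5-point examples rest on assumed rates, and the direction could be either way. Bias in the contrast requires entry to differ between control and intervention time. In a stepped wedge this could arise from a calendar trend; a model with period effects would remove a trend common to all clusters, but not a difference in entry tied to exposure.

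This is a minor matter, worth correcting because the measure is scheduled at every survey and compared between conditions. The primary outcome, the sample size and the secondary outcomes named in the abstract and Table 1 are untouched.

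**What to change.** Keep cluster retention as a cluster-level measure from programme and EMR data, and reword its definition in Table 5 along these lines: patients active at period start who are still active at period end, divided by all patients active at period start, times 100. State that new enrolments and transfers-in are excluded from the numerator, as are returners who were not active at the start. State also that transfers-out, deaths and, if the measure is limited to an age band, ageing-out are counted and reported separately.

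The measure should not be moved to the enrolled participants, because that would replace a cluster-level programme indicator with a different outcome.

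The cost is small: one definition, and a calculation from patient-level lists rather than aggregate programme reports. Study population already describes a central EMR database that produces a line list of all young people at the participating sites, so the data should be available. If a closed group was intended all along, the same rewording makes that explicit.

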### Study tools

#### Patient activation measure

The Patient Activation Measure (PAM) is a tool designed to assess an individual’s knowledge, skills, and confidence in managing their own health and healthcare. The measure evaluates patients across four levels of activation. At Level 1, patients may not yet grasp the importance of their role in managing their own health. Level 2 marks the beginning of confidence and knowledge development, though patients might still struggle with maintaining consistent self-management behaviors. By Level 3, patients have gained key information and are taking action, although they may still need guidance to improve or sustain certain health behaviors. Finally, at Level 4, patients are proactive, able to maintain lifestyle changes, and manage their health independently with minimal support. The Patient Activation Measure (PAM) is typically scored on a 100-point scale, where higher scores indicate greater activation [11].

#### Antiretroviral therapy adherence questionnaire

To assess medication adherence in participants, we will use a customized ART Adherence Questionnaire utilizing a visual analogue scale (VAS) to estimate self-reported adherence over the past 30 days. Similar VAS measures have been well-validated in previous studies, demonstrating their reliability and simplicity for capturing self-reported adherence, particularly in diverse patient populations [12–14]. In addition to the VAS, our tool incorporates questions about the timing of missed doses and the reasons for non-adherence such as being away from home, forgetting, or concerns about side effects. This adherence measure enables both a visual and quantitative reflection of participants’ adherence behaviors, facilitating tracking of adherence patterns across the study. This tool will be administered at 3, 6 and 9 months.

#### Viral load suppression and cluster retention

A customized data collection form will be used to extract individual viral load suppression status, cluster retention and cluster viral load suppression data from program reports and facility EMRs.

#### Evaluating usability

At the end of the intervention period, we will administer the Mobile App Usability Questionnaire (MAUQ) to all users (HCPs and patients). The tool has shown high reliability in prior studies, with Cronbach’s alpha coefficients consistently exceeding 0.80, reflecting strong internal consistency [15]. We have obtained permission to use the MAUQ and will follow standard protocols for its administration and scoring to ensure reliable results in our study.

#### Acceptability survey

The acceptability survey was designed specifically for this study, drawing on validated frameworks for measuring user acceptance and satisfaction [16]. Pilot testing was conducted to refine the survey and ensure its reliability before full-scale administration.

#### Social engagement score

The SSQ6 (Social Support Questionnaire—Short Form) is a well-established tool used to assess perceived social support availability. This tool, which is freely available for research use, measures the number of available supports and rates the participant’s satisfaction with that support [17]. We will track user engagement in online communities and compare it with baseline social engagement scores from the SSQ6. This will involve collecting quantitative data on user interactions and activity levels.

#### Focus group discussions

Focus group discussions (FGDs) will be structured to gather qualitative insights from users about their experience with the portal. Discussion guides have been developed based on key usability and satisfaction themes. We will use trained facilitators to ensure consistency and depth in the discussions. Insights from FGDs will be analyzed thematically to identify common issues and suggestions for improvement. This feedback will be used to inform iterative design enhancements to the portal.

#### Portal-based measures

During the study, technical data related to functionality, stability, fidelity, and quality of the myCareHub platform will be continuously collected. The platform will automatically track key metrics, such as user logins, accessed functions, and time spent on various functional components. This usage data will be continuously analyzed to identify patterns and areas for improvement. Descriptive statistics and usage trends will be reported to highlight key findings related to user behaviour and feature performance.

*Functionality*. We will assess whether myCareHub operates as intended by collecting data through the user experience survey, conducting FDGs (qualitative), and using the Usability section of the MAUQ for both patients and HCPs.

*Usability*. We will evaluate the ease of use of myCareHub by using the Functionality section of the MAUQ tool.

*Stability*. The stability of myCareHub will be measured through system reports on server downtime, server operation capacity, network connectivity, SMS/notification failure rates, and using the Stability section of the MAUQ tool.

*Quality*. To assess the quality of myCareHub, we will measure the average time spent on the portal, frequency of use, and functionalities accessed. Qualitative aspects of portal use will also be examined using the MAUQ tool. Additionally, a mobile health service patient acceptability questionnaire will be administered.

*Fidelity*. We will track whether field implementation alters the functionality and stability of the system by reviewing functionality reports, stability reports, and instances of forgotten passwords or incorrect intervention delivery by HCPs.

*Cost*. A comprehensive cost analysis will be undertaken to estimate the total cost of setting up myCareHub. This will include operational costs, such as server expenses and staff training.

*Additional screening tools*. myCareHub users will have access to various screening tools on their health diary, including the tuberculosis (TB) case finding tool, patient health questionnaire– 9 (depression screening), gender-based violence screening, contraceptive need screening, and screening for alcohol and substance use disorders. These tools are free to use and are already integrated as part of the standard of care within the ART program. Once these tools are completed, HCPs will receive an in-app notification indicating a pending task, with an automated status response sent back to the user. Upon task completion at the clinic, the HCP will mark the task as fulfilled, triggering a second notification to the user. myCareHub will automatically track this process cycle, and at the end of the study, the proportion of services fulfilled through the portal will be summarized and compared with the total services offered to the same age group. The median time to diagnosis of TB through the portal will be calculated and compared to usual care.

